## Abstract

**Introduction:**

Recent evidence has implicated the precuneus of the medial parietal lobe as one of the first brain areas to show pathological changes in Alzheimer’s disease (AD). Damage to the precuneus through focal brain injury is associated with impaired visually guided reaching, particularly for objects in peripheral vision. This raises the hypothesis that peripheral misreaching may be detectable in patients with prodromal AD. The aim of this study is to assess the frequency and severity of peripheral misreaching in patients with mild cognitive impairment (MCI) and AD.

**Methods and analysis:**

Patients presenting with amnestic MCI, mild-to-moderate AD and healthy older-adult controls will be tested (target N=24 per group). Peripheral misreaching will be assessed using two set-ups: a tablet-based task of lateral reaching and motion-tracked radial reaching (in depth). There are two versions of each task, one where participants can look directly at targets (free reaching), another wheren they must maintain central fixation (peripheral reaching). All tasks will be conducted first on their dominant, and then their non-dominant side. For each combination of task and side, a Peripheral Misreaching Index (PMI) will be calculated as the increase in absolute reaching error between free and peripheral reaching. Each patient will be classified as showing peripheral misreaching if their PMI is significantly abnormal, by comparison to control performance, on either side of space. We will then test whether the frequency of peripheral misreaching exceeds the chance level in each patient group and compare the overall severity of misreaching between groups.

**Ethics and dissemination:**

Ethical approval was provided by the National Health Service (NHS) East of England, Cambridge Central Research Ethics Committee (REC 19/EE/0170). The results of this study will be published in a peer-reviewed journal and presented at academic conferences.

Strengths and limitations of this studyThe first study to systematically assess visually guided reaching in patients with cognitive impairment.Includes a simple tablet-based task (lateral reaching) that could be readily translated to clinical settings to assess the presence of peripheral misreaching.Case–control statistical tests of deficit are inherently low powered, so subtle deficits of reaching may not be detected at the level of individual patients.

## Introduction

The pathophysiological cascade that leads to Alzheimer’s disease (AD) can begin up to 20 years before the onset of cognitive problems in both autosomal and sporadic AD.^1–5^ In dominant and early-onset cases, there is evidence that the precuneus is one of the earliest regions to be affected.^5 6^ Focal damage in and around this brain area is known to be associated with deficits of visually guided action.^7^ One example of such a condition is optic ataxia, an impairment of misreaching typically reflected in peripheral vision.^8 9^ Patients with optic ataxia do not often report this symptom and it is rarely assessed in clinical settings, and it can therefore go undetected.^10^ The changes observed in the precuneus in prodromal AD, and the link between the precuneus and optic ataxia, raise the hypothesis that optic ataxic misreaching may be detectable in patients with prodromal AD.

### ​Specific hypothesis

The hypothesis that peripheral misreaching is a feature of AD means that individual patients with AD, and possibly those with mild cognitive impairment (MCI), may show an abnormally large inflation of reaching errors when aiming for targets in peripheral vision, as compared with targets in free vision. At a group level, patients with AD and, to a lesser extent, patients with MCI may show significantly greater peripheral misreaching than healthy controls (HCs).

## Methods

### Study setting

The study is a collaboration between clinicians and University staff at the University of Edinburgh (UoE) and University of East Anglia (UEA). The details of recruitment and site information can be found in the online supplementary materials. Data collection for this study began on 03 October 2019 and 8 of 48 patients have taken part. Data for HCs have already been collected.

10.1136/bmjopen-2019-035021.supp1Supplementary data

### Participants

Patients with a diagnosis of amnestic MCI or typical (amnestic) mild-to-moderate AD will be invited to take part. To ensure mild-to-moderate cases of AD, patients will have a score >50 in the most recent administration of Addenbrooke’s Cognitive Examination (ACE-III).^11^ If there is no recorded ACE-III score, clinical opinion of patient’s condition will be used to assess eligibility.

Older adults without any known neurological disorders will be tested as an HC group. To achieve our target of 24 full datasets per group (Power considerations section), we plan to test up to 30 participants in each group, allowing for possible withdrawals.

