##### ​Visual detection

This is a simple check to confirm that the participant is capable of detecting the targets when presented in peripheral vision, to be allowed for a meaningful test of peripheral reaching (Peripheral reaching section).

Throughout each trial the participant must gaze at the fixation cross. They initiate the trial by pressing and holding down the start box, which disappears when touched. In order to aid the maintenance of fixation, the fixation cross cycles between white and red at the screen refresh rate (60 Hz). After a short delay (250–750 ms), a target can appear at one of the nine locations for 1 s, or no target appears. This is followed by a short beep (100 ms, 440 Hz) to indicate the end of the trial. The participant must verbally report whether or not a target was seen in that interval. The experimenter records the response using the keyboard (‘y’—yes, ‘n’—no, ‘v’ - void). If the participant makes an eye movement, the experimenter presses ‘e’ and the trial is repeated. The block ends after 15 valid (no eye-movement) trials, one for each of the nine target locations, and six catch trials with no target.

To progress to the peripheral reaching task, participants are required to detect at least 6/9 targets and correctly rejects at least 3/6 catch trials. Otherwise, testing is discontinued on that side of space.

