**Figure 3 F3:**
[figure not shown]
Relation between(A) control sample size and power to detect a single-case deficit in a one-tailed test, for different sizes of deficit (D, expressed as SD of control mean). (B) D and power to detect a deficit, given a control sample size of 24, for adjusted (.025) and unadjusted (.05) alpha criteria.

We will next assess, for each side, whether the PMI of controls is related to age or sex, by computing Pearson’s correlations. If the correlation is ≥0.3 on either side, then that variable will be included as a covariate in the subsequent case–control comparisons for both sides.

Case–control comparisons will then be run to compare each patient’s PMI against control performance on each side of space. These comparisons will be based on Crawford and Howell's^15^ modified t-test; or, if covariates are included, we will use the Bayesian Test of Deficit with covariates.^16^ The individual tests will be one-tailed, with an alpha level set to 0.025, in order to constrain per-patient alpha level (across the two sides) to 0.05. If a patient shows a deficit on either side that meets the adjusted criterion (0.025), they will be classified as showing periperheral misreaching. If a patient shows a deficit on either side that would meet the unadjusted criterion (0.05), but not the adjusted criterion, they will be classified as showing borderline peripheral misreaching.

Finally, a binomial test will test whether the rate of observed peripheral misreaching exceeds the rate expected by chance (ie, the per-patient adjusted alpha level of 0.05). A significant outcome (p<0.05) for either patient group will indicate that peripheral misreaching is a feature of this patient group. The observed rate of peripheral misreaching will provide an estimate of how common it is. We will run a further analysis including borderline cases and compare the rate of peripheral misreaching in each patient group against the appropriate chance level of 0.10.

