#### ​Group-level analysis

The case–control approach will be complemented by a group-level analysis of variance (ANOVA) of reaching accuracy, as measured by the PMI, with the between-subject factor of group (HC, MCI, AD) and the within-subject factor of side (non-dominant, dominant). This analysis will test whether the average severity of peripheral misreaching in each patient group significantly exceeds that observed in HCs.

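### Testing can stop on one side, but the full-dataset target, the per-patient alpha and chance levels and the side ANOVA all assume two tested sides, and no rule covers a one-side patient

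*Protocol article*

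**What the plan says.** In the lateral task, the Visual detection section sets a check before peripheral reaching: "participants are required to detect at least 6/9 targets and correctly rejects at least 3/6 catch trials". The consequence of failing is limited to one side: "Otherwise, testing is discontinued on that side of space". A patient can therefore finish with a PMI on one side, on both or on neither.

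The Participants section sets the sample target ("To achieve our target of 24 full datasets per group") and adds: "we plan to test up to 30 participants in each group, allowing for possible withdrawals". It does not define a full dataset.

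Under Analysis of single-case deficits, the per-side rule is: "The individual tests will be one-tailed, with an alpha level set to 0.025". The reason given is "in order to constrain per-patient alpha level (across the two sides) to 0.05". A patient is classified on a deficit on either side. Each patient group's count is then tested against a single chance level, 0.05 in the main analysis and 0.10 when borderline cases are added. The same section uses the observed rate as the estimate of how common misreaching is.

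The Group-level analysis section specifies an ANOVA of the PMI with group between subjects and a "within-subject factor of side (non-dominant, dominant" levels.

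**The concern.** The one-side outcome is built into the testing procedure, and it arises in the lateral task, which Power considerations names as the basis of the main inferential analyses. Every downstream rule is nevertheless written for a patient with two tested sides.

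Two treatments of a one-side patient are possible, and they are alternatives:

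- **Left out.** The binomial rate and the ANOVA describe only patients who could be tested on both sides. That is narrower than the clinical groups for which the rate is meant to be an estimate.
- **Kept.** The patient has one chance of being flagged instead of two, yet is counted against a chance level derived from two.

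If the choice is made after the data are seen, the denominator of the main result becomes a post hoc decision. When the article was written, 8 of 48 patients had been tested, so a rule could still be fixed for nearly all of them.

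**Working it through.** **Inputs from the protocol.** Per-side alpha 0.025 (adjusted) and 0.05 (unadjusted, borderline); per-patient chance levels 0.05 and 0.10; group test at p<0.05; 24 controls; 24 patients per group, up to 30 tested.

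**Assumptions, not in the protocol.** The number k of one-side patients among 24 is varied from 0 to 12. Illustrative deficit D = 2 control SDs, with the patient's score normal and with the control SD.

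**1. The plan's own levels.** With two sides, 0.025 + 0.025 = 0.05 and 0.05 + 0.05 = 0.10. Both reproduce as Bonferroni bounds (independent sides: 1 − 0.975² = 0.0494 and 1 − 0.95² = 0.0975). The stated levels are sound for a two-side patient.

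**2. One-side patient.** Only one test is run, so the chance rate is 0.025 in the main analysis and 0.05 with borderline cases.

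**3. Sensitivity for that patient.** Under the modified t-test with 24 controls, the statistic follows a noncentral t with 23 degrees of freedom and noncentrality D/√(1 + 1/24). For D = 2 this is 2/1.0206 = 1.960. Power is 0.47 at one-tailed 0.025 and 0.60 at 0.05.

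**4. Group test if one-side patients are kept.** Mean chance level, main: [(24 − k) × 0.05 + k × 0.025]/24. With borderline cases: [(24 − k) × 0.10 + k × 0.05]/24. At k = 4 these are 1.10/24 = 0.0458 and 2.20/24 = 0.0917. The exact null count is a sum of independent Bernoulli variables with these unequal probabilities. The plan's uniform levels give cut-offs of 4/24 (main) and 6/24 (with borderline). The table gives the true type I error at those cut-offs, and the cut-off that the exact null would set.

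| k | Mean chance, main | Type I error at ≥4/24 | Exact cut-off, main | Type I error at ≥6/24, borderline | Exact cut-off, borderline |
|---|---|---|---|---|---|
| 0 | 0.0500 | 0.0298 | 4 | 0.0277 | 6 |
| 2 | 0.0479 | 0.0259 | 4 | 0.0228 | 6 |
| 4 | 0.0458 | 0.0223 | 4 | 0.0185 | 6 |
| 6 | 0.0438 | 0.0191 | 4 | 0.0149 | 6 |
| 8 | 0.0417 | 0.0162 | 4 | 0.0118 | 5 |
| 12 | 0.0375 | 0.0113 | 4 | 0.0071 | 5 |

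The main cut-off does not move: at k = 12 the probability of 3 or more is still 0.059. The borderline cut-off falls from 6 to 5 at k = 7, where the probability of 5 or more is 0.048.

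**5. Rate if one-side patients are left out.** As a ceiling, suppose all 6 of the 30 − 24 spare places are lost and 5 of 24 completers are flagged (5/24 = 0.21). The rate over all 30 then lies between 5/30 = 0.17 and (5 + 6)/30 = 0.37. The range spans the 1 in 5 that Power considerations treats as the least prevalence of interest. It is a bound, not a forecast.

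**The case against.** The strongest reply is that this is an unstated handling rule with little numerical effect. Much of that stands.

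- **Replacement.** A reader might infer that incomplete patients are replaced by patients who complete everything. The protocol does not say so. Its only explicit replacement rule is for control outliers, and the margin up to 30 is explained by withdrawals, not detection failures. Classification on either side could equally be read as keeping a one-side patient.
- **Both harms at once.** A reader might infer that the rate is both selected and wrongly referenced. For any one patient only one of the two can apply.
- **Direction.** The mis-reference makes the test stricter and cannot inflate false positives. At the group level it changes no main cut-off for k up to 12.
- **Who is lost.** A reader might infer that the patients stopped on a side are the most impaired, or that fatigue concentrates losses on the non-dominant side, which is tested second. The protocol gives no data on either. The check is lenient, it concerns seeing the target, and significant uncorrected visual impairment is already an exclusion.
- **Missing-data detail.** Handling of incomplete cases in the ANOVA is often left to a fuller document. Taken alone, that part would not be a finding.

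What does not stand is that nothing is wrong. The protocol states the two-side levels and applies them to the whole group, while its own procedure produces patients for whom they are arithmetically wrong. The only way to avoid this is to exclude those patients, which narrows the population that the rate describes.

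**Conclusion.** The concern holds in a limited form. The plan foresees a one-side outcome, but its sample target, alpha and chance levels and ANOVA fit only two-side patients, and it does not say which treatment applies.

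If one-side patients are excluded, the rate and the ANOVA describe two-side completers. If they are kept, their chance rate is half the stated one. The second error is conservative. Its main cost is sensitivity for the individual patient, 0.47 against 0.60 at D = 2, and it moves a group cut-off only in the borderline analysis, from about 7 one-side patients in 24.

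The size of either effect depends on how many patients are stopped on one side, which the documents do not give. The figures also rest on normal control scores, equal SD in patients, and the Bonferroni levels for two-side patients. The point is worth acting on because it settles the denominator of the main result at almost no cost, not because a large bias has been shown.

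**What to change.** 1. Define a full dataset, and state that every patient with a lateral PMI on at least one side enters the binomial denominator.
2. Keep one common per-side threshold for all patients: 0.025, or 0.05 for borderline cases. Relaxing it for one-side patients would recover their sensitivity, but the same result would then count as misreaching in one patient and borderline in another.
3. Refer the observed count to the exact null in which a one-side patient has chance 0.025 (0.05 with borderline cases) and a two-side patient 0.05 (0.10).
4. Fit the group-by-side analysis as a linear mixed model with a random participant effect, so that one-side patients contribute their data.
5. Report the number discontinued per side and group, and show the rate for two-side completers beside the rate for all analysed patients. The second figure is needed because a one-side patient has only one opportunity to be flagged.

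The cost is wording and a different model call, with no extra patients or tests. The drawbacks are a slightly unbalanced model, a binomial reference that is not the standard one, and sensitivity in one-side patients that stays at the 0.025 level.

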#### Inclusion criteria

For all participant groups, the ability to give informed consent is the initial inclusion criterion. Additional inclusion criteria are then applied to each group.

Control group inclusion criteria:

Aged 50–75. (NB. The age-range for controls is targeted at the expected age range for patients, but the allowable range of ages for patients is wider than this, in order not to restrict recruitment unnecessarily.)No reported neurological or neurodegenerative conditions.

MCI group inclusion criteria:

Aged 45–85.Clinical diagnosis of MCI with an amnestic pattern of presentation. This includes an observed deficit on cognitive/neuropsychological testing suggesting amnestic and visuospatial profile deficit, low β-amyloid, elevated phosphorylated Tau, regional atrophy on magnetic resonance brain imaging and/or regional perfusion changes on HMPAO-SPECT (Single photon emission computed tomography with hexamethyl propylenamine oxime).

AD group inclusion criteria:

Aged 45–85.Clinical diagnosis of AD.

#### Exclusion criteria

For all participant groups, the following exclusion criteria are applied:

Significant difficulty communicating or understanding instructions in English.Significant, uncorrected visual impairment (eg, cataract, macular degeneration, scotoma, amblyopia and strabismus).Conditions that could interfere with smooth hand movements (eg, ataxia, essential tremor and severe arthritis).Clinical features suggestive of Lewy body pathology (eg, visual hallucinations or rapid eye-movement (REM) sleep disorder).

#### Public and patient involvement

Patients with MCI or AD and their carers were involved in the early stages of planning and development. A focus group was held at the Anne Rowling Clinic in Edinburgh where patients and carers had the opportunity to try out prototypes of the tablet-based reaching task and provide feedback on task design. This feedback was used to optimise the final task for patient accessibility and clarity.

### Tasks

Two different set-ups will be used to assess peripheral reaching: a tablet-based assessment of reaching in the frontoparallel plane (lateral reaching), and a motion-tracking assessment of reaching in radial depth (radial reaching). Participants will complete two versions of each reaching task: a version in which participants look directly at targets before reaching to them (free reaching); and a version where central fixation is maintained (peripheral reaching). Any general factors affecting motor accuracy should influence both free and peripheral reaching, so we will treat the free reaching condition as a baseline condition, to be subtracted from peripheral reaching performance, to isolate the specific increase in error due to peripheral target presentation.^12^ The critical outcome measure is therefore the inflation of absolute reaching error in peripheral reaching relative to free reaching.

Before testing, the participant’s dominant writing hand is identified (by self-report). All tasks are completed first on the dominant side, using the dominant hand, followed by the non-dominant side and hand. Lateral reaching is completed first, followed by radial reaching. All tasks are performed in the same order for all participants.

#### Lateral reaching tasks

##### Stimuli and apparatus

Stimuli are presented on an HP Pavillion ×360 touch screen (active display 310×175 mm, resolution 1920×1080 pixels). Tasks are controlled by a custom programme written in OpenSesame V.3.2.8 *Kafkesque Koffka*.^13^ Participants are seated 40 cm away from the screen which is positioned with either the right edge (left-sided reaching, figure 1A) or the left edge (right-sided reaching, figure 1B) of the screen aligned to their midline figure 1A
figure 1B. A start box (white rectangle, 2°×2°, 13.96×13.96 mm) is drawn at the edge (right or left) of the screen, aligned to participant’s midpoint. In some tasks (detailed below) a white fixation cross is present (1°×1°, 6.98×6.98 mm), located 34.9 mm (5°) directly above the start box. Targets are white circles (diameter=2°, 13.96 mm) presented along radial spokes at 28°, 33° and 38° to the left (figure 1A) or right (figure 1B) of fixation. The experimenter sits across the table and monitors eye movements directly.

**Figure 1 F1:**
[figure not shown]
Nine target positions for the lateral reaching task for left (A) and right (B) hand sides. At a viewing distance of 40 cm targets are presented at approximately 28°, 33° and 38° of eccentricity.

##### ​Free reaching

For the first block in the lateral reaching task participants are not required to fixate, therefore, the fixation cross is absent.

Participants initiate a trial by pressing and holding down the start box, which disappears at touch. At this point, they may search the screen for a target. After a short delay (250–750 ms, randomised 100 ms intervals), a target appears at one of nine possible locations. As soon as the target appears, participants look at it and make one smooth reach to try to touch the target. The target remains on the screen until a touch is recorded at any location, and then the target disappears and a short beep (100 ms, 440 Hz) is played. The validity of the trial is then coded by the experimenter using a keyboard; ‘y’—valid trial, ‘e’—the participant did not move their eyes to the target, ‘v’—void trial, and the start box reappears to begin another trial.

If an ‘e’ or ‘v’ is pressed, the corresponding trial is repeated until a valid trial is recorded. The block ends after a minimum of 27 valid trials (3 per target location), or after 50 valid and ‘no eye-movement’ trials.

##### ​Visual detection

This is a simple check to confirm that the participant is capable of detecting the targets when presented in peripheral vision, to be allowed for a meaningful test of peripheral reaching (Peripheral reaching section).

Throughout each trial the participant must gaze at the fixation cross. They initiate the trial by pressing and holding down the start box, which disappears when touched. In order to aid the maintenance of fixation, the fixation cross cycles between white and red at the screen refresh rate (60 Hz). After a short delay (250–750 ms), a target can appear at one of the nine locations for 1 s, or no target appears. This is followed by a short beep (100 ms, 440 Hz) to indicate the end of the trial. The participant must verbally report whether or not a target was seen in that interval. The experimenter records the response using the keyboard (‘y’—yes, ‘n’—no, ‘v’ - void). If the participant makes an eye movement, the experimenter presses ‘e’ and the trial is repeated. The block ends after 15 valid (no eye-movement) trials, one for each of the nine target locations, and six catch trials with no target.

To progress to the peripheral reaching task, participants are required to detect at least 6/9 targets and correctly rejects at least 3/6 catch trials. Otherwise, testing is discontinued on that side of space.

